#### Qualitative Data Analysis

Qualitative interviews will be conducted in Nepali and audio-recorded with the participants’ consent. The recordings will be stored on a password-protected device. Transcription will be carried out in Nepali, and then the transcripts will be translated into English. The transcripts will undergo thorough review and validation against audio recordings to ensure accuracy. Qualitative content analysis will be performed. Independent researchers will initially conduct open coding, followed by discussion within the study team. Agreed-upon codes will be grouped into categories and themes, which will be developed and finalized based on the study objectives.

### Monitoring and Evaluation

The monitoring committee will comprise a study principal investigator, coinvestigators, and other independent experts who will oversee the study’s implementation and data collection. Any deviations from the protocol will be identified and documented during monitoring. The team will monitor and supervise field activities and communicate over the phone every day and visit all the study sites every month. The monitoring activities will be aided by checklists, tools, and manuals. Regular communication, both oral and written, will facilitate ongoing monitoring and updates among data collectors, intervention implementers, and other study members at the central offices.

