### Randomization and Blinding

From a sampling frame of 43 health care facilities available in Madhesh Province, a total of 24 (56%) facilities were selected based on the flow of women seeking various health-related services. The selection process involved randomization of health care facilities using a computer-generated random number table, ensuring a 1:1 ratio of intervention and control clusters (12, 50%, intervention and 12, 50%, control clusters). Each health care facility represents 1 cluster.

Participants visiting the intervention sites will be recruited into the intervention arm, while those visiting the control sites will be recruited into the control arm. To maintain blinding, both participants and health care facility staff will be completely unaware of the information pertaining to the 2 different arms, as well as the arm to which their respective health care facility belongs. However, it may not be possible to conceal this information from the study team responsible for the study design. Therefore, the study will be unmasked during data monitoring, evaluation, and analysis.

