### Data Management and Analysis

#### Quantitative Data Analysis

Electronically collected data will be securely stored in a central office cloud, accessible only to designated study team members. Paper-based data pertaining to the study will be secured in a locker and retrieved from data collectors during central study team monitoring. Regular checks will be conducted to ensure data accuracy and quality, with necessary feedback provided to the data collectors. The primary measure of intervention effects will be based on intention-to-treat analyses. Multilevel analysis will be conducted to account for DeVI’s impact on primary and secondary outcomes, adjusting for clustering at the health center level [46]. The model will consider intervention × time interactions to assess the differential effects of DeVI on changes in outcomes from baseline to the final follow-up. Cluster-level variables will also be compared between intervention and control arms since randomization is based on health care facilities. Furthermore, the study will assess variations in outcome measures of interest between urban and rural areas.

The knowledge, perception, and preparedness of both intervention implementers and data collectors will be assessed before and after the training through pre-, post-, and follow-up tests. Quantitative data will be analyzed using STATA 15 software.

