The process evaluation will uncover unforeseen insights, propose solutions, and introduce innovative approaches that encompass diverse aspects and perspectives of health care providers engaged in the trial. Moreover, should the trial deviate from its predetermined trajectory, we will diligently work to enhance the program by addressing areas requiring improvement, facilitating, overcoming barriers, ensuring resource availability, and effectively managing the time of health care providers.

Periodic monitoring will involve conducting site observations, observing intervention sessions with participant consent, and keeping track of participants. Regular meetings will be held between the study team and field teams to exchange updates and monitor progress. Adverse events related to the intervention will be reviewed periodically. The study team will cross-check the collected data for accuracy and completeness. Any identified errors during data monitoring will be promptly addressed through communication with the field teams for correction.

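### The article makes unmasked monitoring and analysis a rule because the designers know the allocation; that does not follow, and it permits investigators on the monitoring committee to see outcomes by arm

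*Protocol article*

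**What the plan says.** All references are to the protocol article.

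- **Randomization and Blinding.** Participants and facility staff are to be kept unaware of the arms. For the designers, the article says that "it may not be possible to conceal this information from the study team responsible for the study design", and goes straight on: "Therefore, the study will be unmasked during data monitoring, evaluation, and analysis". Each facility is one cluster and belongs to one arm.
- **Monitoring and Evaluation.** "The monitoring committee will comprise a study principal investigator, coinvestigators, and other independent experts". The committee's stated task is to oversee how the study is carried out and how data are gathered. The team telephones the field daily and visits every site monthly.
- **Quantitative Data Analysis.** Stored data are "accessible only to designated study team members".
- **Process Evaluation.** "The study team will cross-check the collected data for accuracy and completeness". Also: "Adverse events related to the intervention will be reviewed periodically". And "should the trial deviate from its predetermined trajectory, we will diligently work to enhance the program by addressing areas requiring improvement".
- **Adverse Events and Risk Management.** Site staff notify the project coordinator. The study team guides the response and records the details on an adverse event form. Listed events include serious violence and suicide attempts.
- **Results.** Data analysis starts once all data are in. The only accruing figures shown by arm are enrolment counts: 269 intervention and 309 control.

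**The concern.** The masking sentence reads as a consequence of something unavoidable, but it is a choice, and a wider one than its premise supports. It removes masking from three activities (monitoring, evaluation and analysis) for which masking is at least partly achievable.

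Three features of this trial make that matter:

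- The primary outcomes, psychological distress and intimate partner violence, are self-reported and collected by data collectors at the facilities. Those collectors are in daily contact with the study team. Knowledge of emerging differences could influence coaching, follow-up effort or delivery, even without intent.
- DeVI was developed for this study, and the team revised it after the formative work. The investigators therefore have an interest in the result.
- The article names escalation of violence as a risk to participants. It places the recording and assessment of adverse events with the study team and describes no independent review of them by arm.

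**Working it through.** No arithmetic applies. The check is to set the statements side by side and see what each one supports.

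**1. Premise against conclusion.** Three kinds of information need separating:

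- (a) which facility is in which arm;
- (b) individual records from a known site;
- (c) outcomes or events aggregated by arm.

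The premise, that designers cannot be kept from the allocation, concerns (a) only. The conclusion removes masking for (c) and for the final analysis as well. Nothing in (a) requires that (c) be produced for the investigators before lock, or that the analyst work with uncoded arms.

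**2. What the rule permits.** Because each facility is in a single arm, site plus allocation gives the arm of every record. Designated team members hold the accumulating data, and the study team checks them as they arrive. Anyone with both could tabulate outcomes by arm. The masking sentence allows this, and no other sentence in the article rules it out.

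**3. Who is covered.** The principal investigator and coinvestigators sit on the monitoring committee with independent experts. The article describes no difference between the two groups in what they may see.

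**4. Safety data.** Serious violence is a listed adverse event, and the frequency and intensity of violence is a primary outcome. Adverse events by arm therefore carry information on a primary outcome. The periodic review in Process Evaluation covers events related to the intervention, and neither the reviewer nor the person who judges relatedness is named.

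**5. Programme changes.** The commitment to improve the programme is triggered when the trial departs from its planned course. It carries no condition that the decision be made without outcomes by arm.

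**6. What is not stated.** No sentence has the committee, or anyone else, reviewing accumulating outcomes by arm. No interim comparison or stopping rule is described, and analysis is placed after data collection. The finding is therefore about what the wording permits. It does not show a planned interim look.

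**7. Would masking be possible?** A coded arm variable alone would not be enough. The planned multilevel model needs a facility identifier, and a true identifier reveals the arm to anyone who knows the allocation. PSYCHLOPS forms from the five sessions exist only in the intervention arm and would also reveal it. Facility identifiers must be recoded and the session data left out of the analysis file.

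**The case against.** The strongest reply is that the risk is assembled from several sections and stated in none. The committee's remit is conduct and data collection, the data checks are for accuracy and completeness, and analysis waits for all the data. The programme clause belongs to the process evaluation, speaks of barriers, resources and staff time, and does not mention the committee. It reads at least as naturally as restoring planned delivery as changing DeVI's content. Independent experts are on the committee, and a charter or the full protocol may set out who sees what. There are also real safety procedures: listed event types in both arms, immediate notification, a structured form and specialist referral.

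Most of this stands, and it rules out several stronger readings:

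- A reader might infer that investigators will review results by arm and adjust the programme accordingly. The article does not say so.
- A reader might take the wording of the committee sentence to call the investigators independent. The natural reading is investigators plus independent experts.
- A reader might use the enrolment still outstanding in December 2022 to size the problem. Those counts date no exposure to outcomes by arm.

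The objection does not rescue the masking sentence. That sentence is stated, not omitted, and its reasoning is unsound whatever an unseen charter adds. It is also true that masking a team that knows the site allocation can only be partial. That limits the remedy but does not justify abandoning it.

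**Conclusion.** The concern holds in a limited form. The article derives unmasked monitoring, evaluation and analysis from a premise that does not support it. With investigators on the monitoring committee, the wording permits them to see self-reported outcomes and adverse events by arm during the trial. It does not show that they will.

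The size cannot be quantified. With no interim effectiveness analysis described, there is no inflation of the type I error to calculate; the exposure is to operational bias and to safety review that is not independent. The change is worth making because it is cheap, but the point does not invalidate the design. The verdict assumes that no charter or full protocol already restricts access to outcomes by arm. If one does, the masking sentence should be brought into line with it.

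**What to change.** 1. **Randomization and Blinding.** Replace the final sentence. State that the design team knows the facility allocation, but that outcomes aggregated by arm are withheld from the principal investigator and coinvestigators until database lock.
2. **Monitoring and Evaluation.** State that only the committee's independent experts review outcomes by arm, if any are produced, and all adverse events by arm, not just those judged related. The investigators receive pooled data and reports on study conduct.
3. **Quantitative Data Analysis.** Run the primary analysis on a file with coded arms and recoded facility identifiers, without the intervention-only PSYCHLOPS session data.
4. **Process Evaluation.** Decide any programme change without outcomes by arm, date it, and list it in the trial report.

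The handling of individual adverse events is unchanged.

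**Cost.** Mainly wording, plus separate open and closed reports and a recoded analysis file. The independent experts are already on the committee, but the article does not give their number or expertise, so their capacity for this review should be confirmed. Masking will remain partial, because the team knows the site allocation and reports on conduct by site reveal the arm.

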### Process Evaluation

Concurrently with the trial, we will conduct process evaluation following the implementation component of the UK Medical Research Council’s guidance [47] in order to enhance comprehension of the DeVI’s acceptability among both women experiencing violence (reach) and health care providers. Additionally, we will assess the study’s adherence to the intended plan. The evaluation also aims to explore the barriers to and facilitators of DeVI (adaptations) from the perspective of health care providers, providing information about the possibility of its future sustainability and scalability, considering its effectiveness.

This process evaluation is based on the hypothesis that health care providers can identify women experiencing violence with mild-to-moderate psychological distress and that they can deliver planned counseling sessions and inviting women for further sessions and follow-ups on predetermined dates and times. This evaluation also hypothesizes that health care providers will allocate time for delivering the sessions in intervention sites, as well as conducting baseline and follow-up assessments in both intervention and control sites, in addition to their regular duty.

A mixed methods approach will be used for the process evaluation. Qualitative data will be collected through in-depth interviews with data collectors and intervention implementers at different time points. Quantitative data will be collected using an observation checklist and a 3-month follow-up period. The IDIs with health care providers will explore their experiences in, barriers to, and facilitators of recruiting and retaining women, as well as providing suggestions for improvement. Similarly, the observation checklist will help track their progress and status in the trial thus far, while the practice questionnaire will assess changes in their practice regarding violence identification and management. The practice questions will be derived from the practice section of the PREMIS questionnaire, which was previously used during training as a pretest. Qualitative data will be analyzed using thematic analysis [48], while quantitative data will be simply analyzed using descriptive analysis.

The process evaluation will uncover unforeseen insights, propose solutions, and introduce innovative approaches that encompass diverse aspects and perspectives of health care providers engaged in the trial. Moreover, should the trial deviate from its predetermined trajectory, we will diligently work to enhance the program by addressing areas requiring improvement, facilitating, overcoming barriers, ensuring resource availability, and effectively managing the time of health care providers.

Periodic monitoring will involve conducting site observations, observing intervention sessions with participant consent, and keeping track of participants. Regular meetings will be held between the study team and field teams to exchange updates and monitor progress. Adverse events related to the intervention will be reviewed periodically. The study team will cross-check the collected data for accuracy and completeness. Any identified errors during data monitoring will be promptly addressed through communication with the field teams for correction.

### Dissemination of Findings

Study findings, along with policy recommendations for enhanced collaboration between key stakeholders and increased coverage of IPV/domestic violence and mental health services for women, will be disseminated to relevant provincial and national stakeholders and authorities. The study results and recommendations will reach a wider audience through policy briefs, press releases, workshops, conferences, and scientific publications.

## Results

The trial received funding from the Swedish Research Council in 2019. The goal is to recruit 456 eligible women in each arm. As of December 29, 2022, a total of 269 eligible women were enrolled from the intervention sites and 309 eligible women from the control sites. The trial is currently in the recruitment phase. Data collection is expected to be completed by December 2023. Data analysis will begin shortly after obtaining all the data following the established plan. Regular data cleaning and monitoring are being conducted every day.

## Discussion

### Summary

This cluster-randomized trial aims to implement and evaluate the acceptability, feasibility, and effectiveness of DeVI in addressing psychological distress and enabling the secondary prevention of violence for women experiencing IPV. These interventions will be administered by trained nonspecialist mental health care providers in Madhesh Province, Nepal, at the health care facility level. As of December 29, 2022, the study had enrolled 59% (n=456) of eligible women from the intervention sites and 68% (n=456) of eligible women from the control sites. In low-income settings, such as Nepal, mental health specialists are scarce. Therefore, if this study proves effective, it could provide scientific evidence supporting the integration of mental health services into routine health care facilities in Nepal. This integration aims to prevent the recurrence of violence and address mental health issues among survivors of violence. Additionally, the study can offer valuable insights into how nonspecialist mental health care providers can address mental health problems and violence among women experiencing IPV/domestic violence. DeVI aims to improve access for marginalized women, particularly those who are hard to reach and have experienced IPV/domestic violence, while facing mental health challenges. Throughout the intervention, health care providers and survivors of violence will collaborate actively to address violence and enhance the women’s mental well-being. They will develop customized strategies for self-management of these issues. Investing in women’s health is considered a cost-effective strategy to improve the nation’s overall well-being [49].

We hypothesize that addressing the needs of women experiencing IPV/domestic violence will enhance their mental stability and reduce long-term health risks associated with violence. This study will contribute to bridging existing knowledge gaps by generating scientific evidence for regional policy makers, given the limited availability of data on mental health issues in resource-constrained settings.

The results from DeVI will hopefully support the integration of mental health services into routine health programs in Nepal. It could also add evidence to the global knowledge base on how and whether nonspecialist mental health care providers can be mobilized in addressing mental health problems in settings where IPV/domestic violence prevalence is high and human resources scarce. In addition, if this cluster-randomized trial is proven effective, this concept can be replicated in other LMICs following contextual adaptation and testing in each setting and target population.

### Limitations

Women experiencing violence and eligible for our study may refrain from providing consent due to the fear that their husbands or male partners will subject them to further abuse upon discovering their participation. The dropout rate may be higher due to the associated stigma and the fear of family members, society, and perpetrators. In a patriarchal society, such as Nepal, women are typically accompanied by their in-laws or husbands when seeking basic services at health care facilities, which creates reluctance to disclose issues related to violence or participate in the study.

### Conclusion

This trial aims to present vital evidence for mitigating the impact of intersecting violence and mental health issues among women in Nepal. If the intervention is found to be effective, the study has the potential to offer significant contributions and insights into how nonspecialist mental health care providers can address problems related to IPV and mental health among survivors in low-income settings.

## Abbreviations

ANM: auxiliary nurse midwife
DeVI: Domestic Violence Intervention
GHQ-12: 12-item General Health Questionnaire
FGD: focus group discussion
IDI: in-depth interview
IPV: intimate partner violence
KII: key informant interview
LMIC: low-and middle-income country
MAKS: Mental Health Knowledge Schedule
NGO: nongovernmental organization
PHQ-9: 9-item Patient Health Questionnaire
PM+: Problem Management Plus
PREMIS: Physician Readiness to Manage Intimate Partner Violence Survey
PSYCHLOPS: Psychological Outcome Profiles
PTSD: posttraumatic stress disorder
WHO: World Health Organization
